### Sample size estimation

This RCT is a superiority trial, and an appropriate formula was used to estimate sample size [24]. Based on the results of our preliminary observational study and expert advice, we assume an α of 0.05, a 1 –β of 0.80, a between-group difference in primary outcome (total SQD scale score) δ of 8.0, a pooled standard deviation of 14.5, and an allowable dropout rate of 20%. The total sample size is expected to be 130 (65 in each group).

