## Statistical analysis

Data analysis will be performed with Stata v14.0 (StataCorp LLC, College Station, TX, USA). The main primary outcome analysis will be based on the intention-to-treat data set, where the missing values will not be imputed and the patients who took unscheduled medications will be kept in their original group. We will also perform four sets of sensitivity analyses to test the robustness of the results of the main analyses, including (1) using the per protocol data set; (2) imputing missing data using various methods dependent on the proportion and distribution of the missing data; (3) excluding patients who become aware of the grouping accidentally during the trial, which also aims to estimate the placebo effects; and (4) excluding patients who took unscheduled medications. The analysis of secondary outcomes will be based on the per protocol data set, and the analysis of safety outcomes will be based on the safety data set only, both with no imputation. Interim data analyses will be performed after weeks 8 and 52.

Descriptive analysis will be conducted to explore the means and standard deviations of the continuous variables. We will assess the treatment effects by comparing the mean between-group differences of the continuous endpoints with a normal distribution using the independent *t* test. The skewed continuous variables will be described using medians and interquartile ranges. We will use the Mann-Whitney *U* test to assess the equivalency of the skewed continuous variable distributions. Moreover, we will describe categorical variables through their frequencies and percentages. We will evaluate the between-group differences using Pearson’s chi-square test for the cases with expected counts greater than 5 in more than 20% of cells and greater than 1 in any cell or Fisher’s exact test otherwise. We will perform subgroup analyses stratified by gastric cancer stage and chemoradiotherapy regimen for the primary outcome. We set α = 0.05 as the nominal type I error rate, which will be adjusted for the multiple *t* test using the O’Brien-Fleming group sequential method [25].

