### Data collection and monitoring

All investigators involved in the trial will receive research training based on standard operating procedures. An independent data monitoring committee (DMC) at Jiangxi University of Traditional Chinese Medicine will be founded and be responsible for supervising the entire trial process. Data collection, such as questionnaire surveys, physical examinations, biological samples, and laboratory examinations, will be performed by qualified physicians at each research center. Student volunteers, as clinical research coordinators, from Jiangxi University of Traditional Chinese Medicine will be in charge of contacting patients for timely follow-up. Each research hospital will have a clinical research associate from the Jiangxi University of Traditional Chinese Medicine who will be in charge of monitoring patient compliance and case report form completeness and will address issues during the trial. The original case report forms will be inputted into the online database by two clinical research coordinators in duplicate. Personal information for all patients will be anonymized. The database will be password protected and will be managed by the DMC. An independent analyst will have access to the database only during the data analysis period. The DMC will also have the authority to discontinue the entire trial according to the following standards: (1) HGMX does not show any efficacy toward SQD symptoms up to 8 weeks of follow-up, as indicated by an absolute difference < 5 on the SQD scale score between the two groups (this difference is estimated based on the unpublished results of our other trial assessing HGMX for nonorganic gastrointestinal disorders); (2) HGMX does not show statistically significant efficacy for any outcome up to 52 weeks of follow-up compared with placebo; and (3) any severe AE related to HGMX occurs.

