Based on our pilot observations, many patients undergoing gastrectomy achieved quick remission of their gastrointestinal symptoms with 8 weeks of HGMX treatment. Thus, we decided to use three visits (at weeks 2, 4, and 8) to validate the short-term effects of HGMX, which will also provide data for the early discontinuation of the trial as determined by the DMC. The aim of the visits on weeks 26, 52, 78, and 104 will be to investigate the long-term efficacy and safety of HGMX. To improve long-term patient compliance—the key point for obtaining precise results in this trial—we will only include patients with an ECOG score ≤ 1, which ensures that they have sufficient physical abilities to complete this long-term trial and their gastrointestinal symptoms are mild and tolerable so that the need for additional medicine is infrequent. If this trial proves the efficacy of HGMX in patients with good physical performance, we will consider conducting further trials that focus on patients who have worse physical performance (e.g., ECOG score ≥ 2). Moreover, based on our experience, most patients with gastric cancer will return to the hospital to receive regular postoperative follow-up with their attending physicians. Therefore, we anticipate that good compliance with the protocol can be ensured for most patients during the 2-year follow-up period.

This RCT is one of a series of RCTs (the other two trials will focus on nonorganic gastrointestinal disorders and peptic ulcer diseases) assessing the capacity of HGMX to improve gastrointestinal function and systemic symptoms. Although dietary TCM formulas are widely used in clinical practice in China, RCTs with a rigorous design and long-term follow-up are still lacking. To the best of our knowledge, this RCT will be the first to assess a dietary TCM formula for the management of gastric cancer. The results of the RCTs will provide experience and evidence for developing guidelines and policies for facilitating the reasonable use of dietary TCM formulas.

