### Trial status

The protocol version number is 3.2. Trial recruitment was started on May 22, 2017, and the trial has enrolled 80 patients at the time of manuscript submission. Recruitment is expected to be completed in October 2019.

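### The week-52 discontinuation standard treats statistical non-significance as lack of efficacy; with secondary outcomes unaffected, a product that works as assumed would meet it in roughly 10–36% of trials

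*Protocol article*

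**What the plan says.** The Data collection and monitoring section lists three standards under which the committee has authority to discontinue the entire trial. The second is that "HGMX does not show statistically significant efficacy for any outcome up to 52 weeks of follow-up compared with placebo". It is separate from the first, which concerns an absolute difference below 5 points on the SQD scale up to week 8.

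The Statistical analysis section says "Interim data analyses will be performed after weeks 8 and 52" and adjusts the repeated t tests by the O'Brien-Fleming method. The article does not say whether the week-52 standard uses the nominal or the adjusted level, whether earlier visits count, or how many patients must have reached week 52.

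The Discussion sets out the purpose of the later visits: "The aim of the visits on weeks 26, 52, 78, and 104 will be to investigate the long-term efficacy and safety of HGMX". Under Trial status, recruitment began on 22 May 2017 and "Recruitment is expected to be completed in October 2019".

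**The concern.** A trial sized for 80% power has about a one-in-five chance of missing significance when the assumed effect is real, even with its full evaluable sample. The chance is larger at a stricter interim level or with fewer patients. A standard met whenever significance is missed therefore cannot separate a product that does nothing from one that works and fell short at that look. A confidence limit or conditional power would ask the relevant question: is the effect the trial was designed to find still plausible?

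At stake are the power delivered at week 104 and the long-term comparison that the week 78 and 104 visits are meant to supply.

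**Working it through.** **Inputs** (Sample size estimation): type I error 0.05, power 80%, SD 14.5, dropout 20%, and for the effect "a between-group difference in primary outcome (total SQD scale score) δ of 8.0".

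**Plan's own figure.** n per arm = 2 × (1.960 + 0.842)² × 14.5² / 8² = 51.6, so 52. Then 52/0.80 = 65 per arm, 130 in total. The stated size reproduces with a two-sided 0.05 test.

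**Chance that the primary outcome misses at week 52 when the true difference is 8.** Standard error = 14.5 × √(2/n) and drift = 8/SE. The chance of a miss is Φ(c − drift). The critical value c is 1.96 at the nominal level. For O'Brien-Fleming it is 2.454, which assumes that week 52 is the second of three equally spaced looks.

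| Evaluable per arm | SE | Drift | Miss, c = 1.96 | Miss, c = 2.454 |
|---|---|---|---|---|
| 52 | 2.844 | 2.813 | 19.7% | 36.0% |
| 65 | 2.543 | 3.145 | 11.8% | 24.5% |

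**All outcomes must miss.** Take the five secondary outcomes (SF-36, ECOG, weight, BMI, progression-free survival) as null and independent, each tested at the nominal level. The factor is 0.975⁵ = 0.881. At c = 1.96 this gives 0.197 × 0.881 = 17% (52 per arm) and 0.118 × 0.881 = 10% (65 per arm). At c = 2.454 on the primary it gives 0.360 × 0.881 = 32% and 0.245 × 0.881 = 22%. Correlated secondary outcomes bring the figures back towards the primary-alone values. The span is therefore about 10% to 36%.

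**What moves it** (assumptions stated):
- If significance at week 8 or week 52 counts (same bound at both, within-patient correlation 0.5–0.9), the primary alone misses in 9–15% (nominal) or 20–29% (2.454) with 52 per arm, and in 4–8% or 12–19% with 65.
- If five secondary outcomes have true effects of 0.2–0.3 SD (correlation 0–0.5, 52 per arm), the nominal figure is about 3–17%.
- If only 26–40 per arm have week-52 data, the primary alone misses in 31–49% (nominal) or about 50–68% (2.454).

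**What counts as no significant efficacy on the primary outcome** (52 per arm). The limits are 1.96 × 2.844 = 5.6 points and 2.454 × 2.844 = 7.0 points, that is 70% and 87% of the design difference. The week-8 standard treats only differences below 5 as no efficacy.

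**Power lost.** Assume 52 per arm, a difference of 8 at both visits, between-visit correlation 0.5–0.9 and a week-104 test at 1.96. The bivariate normal probability of missing at week 52 but being significant at week 104 is 5–11% at c = 1.96 and 17–23% at c = 2.454. If the committee always acted on the primary outcome, power would fall from 80.3% to about 69–75%, or to about 57–63%.

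**Timing of the look.** Assume uniform accrual over 29 months and ignore dropout.
- Look when the last patient reaches week 52 (month 41): patients who entered in the first 17 months have finished, 17/29 = 59%. Remaining exposure is (12/29) × (6/24) = 10%. With 52 evaluable per arm in a complete trial, about 0.59 × 52 ≈ 30 per arm have week-104 data. Drift is then 2.137 and power about 57%.
- Look when three quarters have reached week 52 (month 33.75): 9.75/29 = 34% have finished and about 27% of exposure remains.
- Look when half have reached week 52 (month 26.5): 2.5/29 = 9% have finished and about 50% remains.

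**The case against.** **The standard is permissive.** The committee has authority to stop, not a duty. This stands: the percentages are chances of meeting the standard, not of stopping. A reader might infer that a working product will be stopped that often, and the document does not say so.

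**Every outcome must fail.** The trial also aims to improve quality of life, performance status and prognosis, so a product that works may well show something elsewhere. This stands too. The 10–36% holds only with secondary outcomes unaffected and the week-52 visit alone counted, and it is not a bound in either direction.

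**The power cost is smaller than the miss probability.** Weeks 52 and 104 measure the same patients, so many trials that miss at the first would also miss at the second. This is correct, and the 5–11% and 17–23% already allow for it.

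**Two harms should not be added together.** A reader might infer that a stop both loses the 2-year question and spares almost no exposure. These belong to different timings. A late look leaves about 10% of exposure and weakens the 2-year comparison. An early look largely removes that comparison but saves 27–50% of exposure.

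**The any-outcome clause also errs the other way.** With six independent null outcomes at one visit, 1 − 0.975⁶ = 14% of ineffective trials would show a chance finding and continue. This is a minor point: such a trial only runs to its planned end, and weight and BMI are nearly one outcome.

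**The level and timing may be fixed in the full protocol or a committee charter, which are not shown.** That would narrow the range. It would not make non-significance a sound futility criterion.

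**Conclusion.** The point holds in this limited form. The week-52 standard, as stated, takes interim non-significance as lack of efficacy. Under the design difference of 8 and SD of 14.5, with secondary outcomes unaffected and the week-52 visit counted, it would be met in roughly 10–36% of trials. Counting week 8, or real secondary benefit, lowers this; an early look raises it. With 52 per arm, observed differences up to 5.6 or 7.0 points would count as no significant efficacy on the primary outcome.

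If the committee acted on the primary outcome, 5–11% (nominal) or 17–23% (O'Brien-Fleming) of trials would be stopped that would have succeeded at week 104. These figures rest on the assumed look spacing, the assumed between-visit correlation and a difference of 8 at both visits. The document does not support saying that the 2-year question is always lost, or that a stop is obligatory. The standard should be changed, but the point does not invalidate the design.

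**What to change.** Replace the second discontinuation standard with a futility guideline on the SQD primary outcome only, kept advisory as now. For example: consider stopping only if the upper 95% confidence limit for benefit at week 52 is below the design difference of 8. State that non-significance alone is not a reason to stop, and state how many patients must have reached week 52.

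With 52 per arm this requires an observed difference below 8 − 1.96 × 2.844 = 2.4 points. It is met in about 2.5% of trials if the true difference is 8, whatever the number per arm.

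The cost is a short edit to the protocol and to any committee charter. The downside is that an ineffective trial is somewhat less likely to be stopped at week 52. With no true effect and 52 per arm, the guideline is met in Φ(2.43/2.844) = 80% of trials. The present standard is met in 0.975⁶ = 86% with six independent outcomes at the nominal level.

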### Compliance and withdrawal

To improve patient compliance, we will offer all test samples (HGMX and placebo) and scheduled examinations free of charge, and patients will receive a travel allowance of 100 yuan at each visit. At the recruitment stage, researchers will emphasize the length of the 2-year treatment and follow-up to patients who are willing to join the trial. The patients will be allowed to complete each follow-up within ±3 days of the scheduled date for the weeks 2, 4, and 8 visits and within ±7 days for the weeks 26, 52, 78, and 104 visits. The used packaging bags will be reclaimed to check patients’ compliance.

Patients will be withdrawn from the trial for the following reasons:Cancer progression and restarting of radiotherapy or chemotherapyRecurrence of surgical complicationsContinuous deterioration of SQD symptomsPoor compliance, indicated by the use of less than 80% of the prescribed trial drug or more than two missed visitsActive withdrawal. Patients can actively withdraw from the trial at any time for any reason, and subsequent treatment will not be affected

## Discussion

Some previous RCTs assessed the effects of Shen Ling Bai Zhu San, the basic formula of HGMX, for treating patients with gastric cancer. These RCTs showed promising results, such as reduction in the incidence and severity of postoperative ileus, irritable bowel syndrome, and anemia [26], remission of gastrointestinal symptoms [27], and improvement in quality of life [28], which could also support the efficacy of HGMX to some degree. However, all of these RCTs had a short treatment course (≤ 8 weeks) and were at high risk of selection and performance bias due to a lack of reporting of information regarding allocation concealment, blindness, and data monitoring. Therefore, high-quality RCT evidence is warranted regarding the efficacy of HGMX for patients who have undergone radical gastrectomy for gastric cancer.

This RCT aims to clarify whether HGMX, as a dietary formula based on TCM theory, is effective and safe for improving SQD syndrome, quality of life, performance status, and prognosis of patients with gastric cancer who have undergone radical gastrectomy. To improve the quality of study reporting and conduct, we will develop a standard operating procedure manual according to the principles of the Consolidated Standards of Reporting Trials Extension for Chinese Herbal Medicine Formulas [29] and will thoroughly train all investigators. A potential limitation of this trial is that we will use a modified version of the classic SQD scale that has not been validated (no reliability or validity evaluation).

Based on our pilot observations, many patients undergoing gastrectomy achieved quick remission of their gastrointestinal symptoms with 8 weeks of HGMX treatment. Thus, we decided to use three visits (at weeks 2, 4, and 8) to validate the short-term effects of HGMX, which will also provide data for the early discontinuation of the trial as determined by the DMC. The aim of the visits on weeks 26, 52, 78, and 104 will be to investigate the long-term efficacy and safety of HGMX. To improve long-term patient compliance—the key point for obtaining precise results in this trial—we will only include patients with an ECOG score ≤ 1, which ensures that they have sufficient physical abilities to complete this long-term trial and their gastrointestinal symptoms are mild and tolerable so that the need for additional medicine is infrequent. If this trial proves the efficacy of HGMX in patients with good physical performance, we will consider conducting further trials that focus on patients who have worse physical performance (e.g., ECOG score ≥ 2). Moreover, based on our experience, most patients with gastric cancer will return to the hospital to receive regular postoperative follow-up with their attending physicians. Therefore, we anticipate that good compliance with the protocol can be ensured for most patients during the 2-year follow-up period.

This RCT is one of a series of RCTs (the other two trials will focus on nonorganic gastrointestinal disorders and peptic ulcer diseases) assessing the capacity of HGMX to improve gastrointestinal function and systemic symptoms. Although dietary TCM formulas are widely used in clinical practice in China, RCTs with a rigorous design and long-term follow-up are still lacking. To the best of our knowledge, this RCT will be the first to assess a dietary TCM formula for the management of gastric cancer. The results of the RCTs will provide experience and evidence for developing guidelines and policies for facilitating the reasonable use of dietary TCM formulas.

### Trial status

The protocol version number is 3.2. Trial recruitment was started on May 22, 2017, and the trial has enrolled 80 patients at the time of manuscript submission. Recruitment is expected to be completed in October 2019.

## Data Availability

Not applicable.

## Abbreviations

AE: Adverse event
DMC: Data monitoring committee
ECOG: Eastern Cooperative Oncology Group
HGMX: Hou Gu Mi Xi
RCT: Randomized controlled trial
SAE: Severe adverse event
SPIRIT: Standard Protocol Items: Recommendations for Interventional Trials
SQD scale: Spleen Qi Deficiency Symptoms Grading and Quantifying scale
SQD: Spleen qi deficiency
TCM: Traditional Chinese medicine
ULN: Upper limit of normal
